## Abstract

**Background:**

Depression is the most common psychiatric disorder reported among patients living with Human Immunodeficiency Virus (HIV), resulting from the intricate combination of biological, psychological, and social factors. Biopsychosocial factors can significantly impact the psychological well-being of men who have sex with men (MSM) living with HIV through social stigma, access and compliance to care, economic insecurity, relationship difficulties, and risky behavior. Compared to MSM without HIV, MSM living with HIV were more likely to be depressed. Despite specific vulnerabilities and health needs, MSM living with HIV remain understudied and underserved in Malaysia owing to legal, ethical, and social challenges.

**Objective:**

This is merely a published protocol, not the findings of a future study. This study aims to determine and explain the predictors of depressive symptoms among MSM living with HIV. Specifically, this study wants to determine the association between depressive symptoms among MSM living with HIV and biological, psychosocial, and social factors. Finally, the mixed methods will answer to what extent the qualitative results confirm the quantitative results of the predictors of depressive symptoms among MSM living with HIV.

**Methods:**

The study has ethical approval from the Medical Research Ethics Committee (MREC) of the Ministry of Health (MOH) NMRR ID-21-02210-MIT. This study will apply an explanatory sequential mixed methods study design. It comprised two distinct phases: quantitative and qualitative study design for answering the research questions and hypothesis. This study will randomly recruit 941 MSM living with HIV in the quantitative phase, and at least 20 MSM living with HIV purposively will be selected in the qualitative phase. The study will be conducted in ten public Primary Care Clinics in Selangor, Malaysia. A self-administered questionnaire will gather the MSM’s background and social, psychological, and biological factors that could be associated with depressive symptoms. For the quantitative study, descriptive analysis and simple logistic regression will be used for data analysis. Then, variables with a P value < 0.25 will be included in multiple logistic regression to measure the predictors of depressive symptoms. In the qualitative data collection, in-depth interviews will be conducted among those with moderate to severe depressive symptoms from the quantitative phase. The thematic analysis will be used for data analysis in the qualitative phase. Integration occurs at study design, method level, and later during interpretation and report writing.

**Result:**

The quantitative phase was conducted between March 2022 to February 2023, while qualitative data collection is from March 2023 to April 2023, with baseline results anticipated in June 2023.

**Conclusion:**

In combination, qualitative and quantitative research provides a better understanding of depressive symptoms among MSM living with HIV. The result could guide us to provide a comprehensive mental healthcare program toward Ending the AIDS epidemic by 2030.

## Introduction

Globally, over 264 million individuals suffer from depression, which is characterized by constant sorrow and a loss of pleasure or interest in activities that were before satisfying or enjoyable [1]. Depressive symptoms are generally known by the SIGECAPS mnemonic: sleep disorders (increased or decreased); interest shortfall; guilt (worthlessness, hopelessness, regret); energy shortage; concentration deficiency; appetite disorder (decreased or increased); psychomotor sluggishness or agitation; and suicidality. The presence of four SIGECAPS symptoms plus depressed mood or anhedonia suggests depression, and further screening should be considered [2]. Depression is distinct from regular mood swings and quick emotional reactions to ordinary stresses. It can be a serious health issue, mainly when persistent and moderate or severe [3]. Among persons with Human Immunodeficiency Virus (HIV) infection, depression is the most commonly documented psychological condition [4]. In a systematic review and meta-analysis, the pooled prevalence of depression among men who have sex with men (MSM) worldwide was 35%. Further continent analysis showed that Asian MSM had the highest pooled prevalence of depression at 37% [5]. Compared to MSM without HIV, MSM living with HIV were more likely to be depressed, with 43% to 58% depression prevalence based on the previous systematic review and study [6, 7].

By 2030, MSM are projected to account for the largest share of prevalent HIV infections in Malaysia, according to Asian Epidemic Modelling (AEM) [8]. In Malaysia, there was an estimated 220,000 MSM population with 21.6% HIV prevalence, making it the highest among other key populations: female sex workers (6.3%), transgender women (10.5%), and people who inject drugs (13.5%) [9]. Regarding depression, to date, the study involving MSM in Malaysia with the highest number of participants was conducted involving 622 mixed MSM with and without HIV status, where 60.8% of them had Center for Epidemiologic Studies Depression (CES-D) scores of ≥ 16, indicating major depression symptoms [10]. However, in this study, the Patient Health Questionnaire-9 (PHQ-9) is utilized since it is half the length of the CES-D, is readily administered and scored, and is increasingly used across various patient groups in research and clinical settings [11].

Depression among MSM has significant effects on public health. Depression affects physical, educational, social, economic, psychological, and short- and long-term health effects for MSM living with HIV [12]. The presence of depressive symptoms may reduce an individual’s motivation to engage in self-care and thus increase the likelihood of risky behavior and suicide [13, 14]. Among MSM living with HIV that have compulsive sexual behavior, having sex can become an alternative strategy to cope with negative emotions such as loneliness, anxiety, and stress [15]. Regarding viral load suppression, depression is a risk factor for ‘imperfect’ antiretroviral therapy (ART) adherence among MSM living with HIV that could jeopardize the Treatment as Prevention (TasP) strategy [16]. More importantly, the co-occurrence of HIV and depression was related to adverse health outcomes, such as low quality of life and deterioration of disease conditions [17].

A complicated combination of biological, psychological, and social variables could cause depression [3]. Therefore, the biopsychosocial approach has been used to structure guidelines, is used clinically, and discusses person-centered care, which can improve patient outcomes [18, 19]. The factors that increase depression among MSM living with HIV include younger age, unemployment, smoking, externalized HIV stigma, not being on ART, lack of self-efficacy, and low social support [20]. In addition, MSM are prone to mental health problems owing to sexual minority stress, homophobia, persecution based on sexual orientation, and stigmas that prevent healthy behavior [21, 22].

Addressing the mental health concerns of individuals living with HIV is essential to providing quality HIV care [9]. In many low and middle-income countries, MSM have fewer resources and are more likely to be hidden and stigmatized, compounding HIV acquisition and transmission risks and limiting access to the most basic services [23]. Continuing research, additional resources, political will, policy change, institutional transformation, community participation, and strategic planning and programming will be required to combat the increasing prevalence of depression among MSM living with HIV.

Despite specific vulnerabilities and health needs, MSM living with HIV remain understudied and underserved in Malaysia owing to legal, ethical, and social challenges. Considering the negative effects of depression on health outcomes and well-being, the determinants of depressive symptoms need to be explored for this vulnerable population. Mental health information from MSM living with HIV can be an important data source to complement existing research on HIV and mental health. The information can aid medical professionals and researchers in understanding the mental health challenges faced by the MSM living with HIV. The relevant bodies can gain insights into mental health needs and develop more effective interventions to address those needs by collecting and analyzing mental health information from MSM living with HIV. Furthermore, the information can inform public health policies and programs and improve the quality of care for MSM living with HIV. Finally, medical professionals can use this information to identify and treat mental health problems in their patients, ultimately leading to better overall health outcomes to support ending the AIDS epidemic by 2030.

This study used a mixed methods design as it can help explore complex phenomena such as depressive symptoms among MSM living with HIV/AIDS. This type of study is intended to give a deeper insight into a topic or issue than qualitative or quantitative research alone [24]. Researchers can use all the data collection tools available rather than being restricted to those types typically associated with quantitative or qualitative research [25]. The study will use the biopsychosocial model as the theoretical framework to guide quantitative and qualitative phases. This framework incorporates biological, psychological, and social aspects to explain the intricacies and evolution of human behavior [26]. It is supposed to obtain information from the MSM’s perspectives and experiences and focus on individual determinants of behavior related to depressive symptoms. Therefore, the protocol was set up to understand the predictors of depressive symptoms among MSM living with HIV and to discuss its relevance due to the negative impacts of depressive symptoms.

### Hypothesis

Hypothesis 1: There is a significant association between social factors and depressive symptoms among MSM living with HIV.

Hypothesis 2: There is a significant association between psychological factors and depressive symptoms among MSM living with HIV.

Hypothesis 3: There is a significant association between biological factors and depressive symptoms among MSM living with HIV.

## Materials and methods

This study has ethical approval from the Medical Research Ethics Committee (MREC) of the Ministry of Health (MOH) NMRR ID-21-02210-MIT. All information obtained in this study is confidential under applicable laws and regulations. No MSM’s personal information will be published when publishing or presenting the study results. Individuals involved in the study and participating medical clinics, qualified monitors, auditors, the sponsor or its affiliates, and governmental or regulatory authorities may inspect and request a copy of medical records, where appropriate and necessary. Permission from the Director-General of Health, Malaysia, or relevant authorities will be obtained before publication. As part of the rights of the MSM as study subjects, they are permitted access to personal data obtained concerning them [27].

### General objective

To determine and explain the predictors of depressive symptoms among MSM living with HIV in Selangor.

### Specific objectives for quantitative study

To determine the prevalence of depressive symptoms among the MSM living with HIV in Selangor.To describe the distribution of biological, psychological, and social factors of depressive symptoms among MSM living with HIV in Selangor.To determine the association between biological, psychosocial, and social factors and depressive symptoms among MSM living with HIV in Selangor.

### Specific objective for the qualitative study

To explain further how the predictors influence depressive symptoms among MSM living with HIV in Selangor.

### Specific objectives for the mixed methods study

To determine to what extent the qualitative results confirm the quantitative result of the predictors of depressive symptoms among MSM living with HIV in Selangor.

### Study design

This study will apply an explanatory sequential mixed methods study design. There will be two main phases of execution, namely quantitative and qualitative study design for answering the research questions and hypothesis. A mixed methods study design is a type of research defined as combining research design and philosophical orientation by the researcher. The core components include a vibrant data collection and analysis of both study designs in response to the research question and hypothesis, combining both findings and implementing comprehensive methods into the specific study design to provide a logical approach within the philosophy framework. The study begins with quantitative data collection and data analysis. In the second phase, qualitative data will be collected and evaluated to explain or expand upon the quantitative results gained in the first phase. Qualitative data collection will be an in-depth interview with the MSM with moderate to severe depressive symptoms from the phase one study. The predictors of depressive symptoms will be further explained by the qualitative design. Data will be mixed by integrating quantitative and qualitative analysis while examining the study’s findings and reaching conclusions.

This study applies integration at all study stages, where it occurs during study design, methods level, and interpretation and reporting levels. Regarding study design, the researcher gathers and analyzes quantitative data first, then uses those results to guide the collection and analysis of qualitative data. Meanwhile, integration at the methods level occurs through connecting, building, and merging approaches. The connecting approach occurs when the interview MSM are selected from those who responded in the quantitative phase. Integration through building occurs when the results from the quantitative phase inform the data collection approach for the qualitative phase, where the selected MSM will be those with PHQ-9 scores ≥ 10. Integration through data merging occurred in this study when parallel questions with the quantitative phase were used in the qualitative phase. The researchers also will merge the PHQ-9 scores and MSM interview data to understand better how qualitative results explain quantitative results. Finally, integration at the interpretation and reporting level occurs when the researchers combine the data through a joint display table. The table will have three columns: (1) Quantitative results; (2) Qualitative interview explaining quantitative results; and (3) How qualitative findings help to explain quantitative results.

Pragmatism is a choice paradigm in this sequential explanatory sequential mixed methods study. It combines objective and subjective evidence that makes this design suitable for explaining complicated issues in public health, such as depressive symptoms among the MSM population. Fig 1 shows the Conceptual framework of explanatory sequential mixed methods study design on predictors of depressive symptoms among MSM living with HIV. Phase 1 will be the quantitative data collection, followed by the interface point. The MSM with moderate to severe depressive symptoms will be identified. The study then enters phase two, where qualitative data collection using an in-depth interview will be carried out among the MSM with moderate to severe depressive symptoms.

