### Qualitative data collection method and process

#### Interview guide for in-depth interviews

The development of the interview guide for the in-depth interview is based on the biopsychosocial approach to help explain why the independent variables tested in the first phase were significant predictors of depressive symptoms. The interview protocol will next be tested on a subset of MSM from the pilot quantitative study with moderate to severe depression. This procedure will improve the quality of the questions through the MSM’s input and the interviewer’s familiarity with the questions.

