#### Study sampling and procedure for qualitative phase

Purposive sampling will be chosen in the qualitative phase. The MSM will be chosen from those with moderate to severe depressive symptoms or those with a PHQ-9 score of ≥ 10 from the quantitative study. Sample size guidelines suggested an adequate range between 20 and 30 interviews [35]. Therefore, 20 MSM will be selected for the qualitative study. Suppose all or most MSM in the quantitative phase have moderate to severe depressive symptoms. Those with severe depressive symptoms will be chosen first, followed by moderately severe depressive symptoms and moderate depressive symptoms. The justification for this method is that the quantitative and qualitative data and their analysis might clarify and explain the statistical results through a more in-depth examination of the MSM’s perspectives.

The study sampling is relatively small compared to the quantitative method, as it depends on the saturation point where no new information is acquired from the following interview. Data saturation is achieved when: (1) there is adequate information to replicate the study; (2) when the capacity to acquire new information has been attained; and (3) when further coding is no longer feasible [36].

Only the main researcher will conduct the in-depth interview for the qualitative study. The researcher will approach the selected MSM at the clinic during clinic visits. The researcher will explain the study protocol and obtain written consent from the participants after a clinic appointment in the consultation room or any available room in the clinic. The room used for the interview will be identified prior to the interview with permission from the clinic’s head. Subsequently, an in-depth interview will be conducted to obtain the information required and will be voice recorded using two voice recorder devices. The interview will require MSM to tell their experiences regarding their depressive symptoms according to the biopsychosocial approach.

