#### Transferability

Transferability reflects the general nature of the study. Transferability is established by presenting proof that the findings of the research study are applicable to others. The applicability can be achieved by a detailed description of the research process, such as research location, sampling method, and population sampling, as well as the study’s outcome, together with evidence of the quotation from the MSM, including the field note [44, 46].

In this study, the qualitative study phase will be started after the data collection and the analysis of the quantitative phase. The MSM with moderate to severe depressive symptoms from the quantitative phase will be involved in the interviews. Hence, during phase one (quantitative) of data collection, a good rapport and healthy relationship will be established between the researcher and the MSM. After each interview, a qualitative study analysis will be conducted to look for any new information that can be included for further analysis. The data analysis result will be explained using the pre-determined themes from the predictors of the quantitative phase. It will be interconnected with subthemes, categories, and coding from the MSM’s quotes.

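### The mixed-methods objective asks how far the interviews confirm the predictors, but the stated procedure leans towards confirmation and has no field or criterion to record disagreement

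*Protocol article*

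**What the plan says.** The section Specific objectives for the mixed methods study, echoed in the abstract's objective, sets this aim: "To determine to what extent the qualitative results confirm the quantitative result of the predictors of depressive symptoms". Explaining how the predictors work is a separate aim, given under Specific objective for the qualitative study.

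Four places describe how the answer will be produced:

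- **Interview guide for in-depth interviews.** The guide follows the biopsychosocial approach and is meant to "help explain why the independent variables tested in the first phase were significant predictors of depressive symptoms".
- **Transferability.** "The data analysis result will be explained using the pre-determined themes from the predictors of the quantitative phase".
- **Study design.** The joint display has three columns. The first holds the quantitative results, the second is headed "2) Qualitative interview explaining quantitative results" and the third "3) How qualitative findings help to explain quantitative results".
- **Study sampling and procedure for qualitative phase.** "The MSM will be chosen from those with moderate to severe depressive symptoms or those with a PHQ-9 score of ≥ 10".

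Other places describe a more open process. Data analysis for qualitative study lets codes and categories arise from the transcripts, with three coders. Table 1, under Steps in qualitative data analysis, puts coding first and forms themes by merging codes. Transferability also has each interview examined for new information. The Discussion expects the joint display to bring out new insights.

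**The concern.** A question about the extent of confirmation needs at least three possible answers: confirmed, partly confirmed, not confirmed. The article names a guide, a source of themes and a display, and each is worded as though the predictor already stands and only its explanation is wanted. Nothing says what would count as confirmation, or where a contrary or absent finding would be entered.

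The Discussion gives the interviews a role in judging the validity of the quantitative results, and it wants interventions that target the predictors. If a predictor is reported as borne out by interviews under a procedure that had no place to record the opposite, that support will carry more weight with readers than it has earned.

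**Working it through.** No arithmetic applies. The check is to set the objective beside each step that produces its answer, and then to ask where each possible finding would be recorded.

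**Step 1: the objective against the steps.**

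- *Objective:* extent of confirmation, hence a graded judgement.
- *Guide:* its stated purpose is to find out why variables were significant. It does not ask whether the men see them as relevant. The biopsychosocial framing is broader than this purpose, so other factors can come up.
- *Themes:* Transferability takes them from the predictors. Data analysis for qualitative study and Table 1 build them from codes. The article does not say which governs.
- *Display:* both qualitative columns are headed as explanation. None is a judgement of agreement.

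**Step 2: where each possible finding would go under the three columns as headed.**

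| Finding | Place in the display |
|---|---|
| Interviews support a predictor | Columns 2 and 3, as headed |
| Interviews support it and add a mechanism | Columns 2 and 3, as headed |
| Interviews point the other way | Could be written as free text in column 2 or 3, against their headings; no class for it |
| Nobody raises the predictor | A thin or empty cell; no class for it |
| A theme matches no predictor | No quantitative result to put in column 1; no row provided for |
| A measured factor that was not retained | Allowed, since column 1 is headed only as quantitative results, but not called for |

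The first two findings have a natural place. The other four can be accommodated only by improvising.

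**Step 3: is a negative answer excluded?** No. Open codes may contradict a predictor, and a predictor theme without supporting quotations would itself suggest non-confirmation. What is missing is a stated way to turn either into an answer to the objective.

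**Step 4: the interview sample.** All interviewees have a PHQ-9 score of 10 or more, so the interviews offer no contrast with men below the cut-off. This adds somewhat to the tilt, but the conclusion does not depend on it.

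**The case against.** The strongest reply is that the article is more open than the four quoted places suggest. Codes and categories may arise from the data, and Table 1 codes before it forms themes. New information is sought after each interview. The Discussion says the two datasets are combined after each phase has been studied on its own. The guide rests on the biopsychosocial approach, and the men are asked about their experience in that frame. All of this stands. It means that a reader who infers that confirmation is guaranteed, or that the objective cannot be answered at all, goes further than the text allows.

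A reader might also infer that every row of the display will be a significant predictor and that none could be shown as contradicted. The article fixes the columns and is silent on the rows, so that does not follow.

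A third tempting inference is that the P < 0.25 screen will feed false-positive predictors into the interviews, to be reported as confirmed. Under Data analysis for quantitative study, 0.25 only governs entry to the multiple regression and significance is set at 0.05. The document gives no basis for calling such predictors likely.

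Two further replies carry less weight. One is that an explanatory sequential design exists to explain. That is so, and the display would suit an objective of explanation alone. That aim is already covered by the qualitative objective, while the mixed-methods objective adds confirmation. The other is that a journal article leaves detail to the full protocol. But this article does not leave the matter open: it names three columns and states where the themes come from. The point concerns what those statements fix.

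**Conclusion.** The point holds in a limited form. The procedure as described favours confirmation, and no field or criterion records discordance or silence, so the mixed-methods objective has no stated route to a graded or negative answer. The article also gives two accounts of where themes come from, and these need to be reconciled.

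The size cannot be put as a number. The weakness touches the mixed-methods objective and the claims built on it; the prevalence estimate, the regression and the qualitative objective of explaining predictors are unaffected. The conclusion assumes that the display will be used with the columns as listed, and that no unpublished rule for judging agreement sits behind them. Because the change is small and lets the study answer its own question, it should be made before the joint display is compiled.

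**What to change.** 1. Reconcile Transferability with Data analysis for qualitative study and Table 1, so that transcripts are coded openly first and the codes are mapped to the predictors afterwards.
2. Add a fourth column to the joint display that classes each predictor as confirmed, expanded, discordant or not raised, with a short written criterion for each class.
3. Add rows for themes that match no predictor and for measured factors that were not retained in the model.
4. Answer the mixed-methods objective from that column.

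Counts of interviewees behind each class, or the share of predictors in each, are optional; with about 20 purposively chosen men they would be descriptive only.

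The cost is a little more coding and reporting work: one column, some rows and one fixed order of steps. No new interviews or staff are needed.
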